## Abstract

**Background:**

In the United States, there has been a concerning rise in the prevalence of opioid use disorders (OUD) among transition-age (TA) adults, 18 to 25-years old, with a disproportionate impact on individuals and families covered by Medicaid. Of equal concern, the treatment system continues to underperform for many young people, emphasizing the need to address the treatment challenges faced by this vulnerable population at a pivotal juncture in their life course. Pharmacotherapy is the most effective treatment for OUD, yet notably, observational studies reveal gaps in the receipt of and retention in medications for opioid use disorder (MOUD), resulting in poor outcomes for many TA adults in treatment. Few current studies on OUD treatment quality explicitly consider the influence of individual, organizational, and contextual factors, especially for young people whose social roles and institutional ties remain in flux.

**Methods:**

We introduce a retrospective, longitudinal cohort design to study treatment quality practices and outcomes among approximately 65,000 TA adults entering treatment for OUD between 2012 and 2025 in New York. We propose to combine data from multiple sources, including Medicaid claims and encounter data and a state registry of substance use disorder (SUD) treatment episodes, to examine three aspects of OUD treatment quality: 1) MOUD use, including MOUD option (e.g., buprenorphine, methadone, or extended-release [XR] naltrexone); 2) adherence to pharmacotherapy and retention in treatment; and 3) adverse events (e.g., overdoses). Using rigorous analytical methods, we will provide insights into how variation in treatment practices and outcomes are structured more broadly by multilevel processes related to communities, treatment programs, and characteristics of the patient, as well as their complex interplay.

**Discussion:**

Our findings will inform clinical decision making by patients and providers as well as public health responses to the rising number of young adults seeking treatment for OUD amidst the opioid and polysubstance overdose crisis in the U.S.

## Introduction

Transition-age (TA) adulthood—18 to 25-years old—is a distinct developmental phase during which a person’s biological, psychological, and sociological aspects are evolving [1–4]. TA adults differ from adolescents in that their brain development is further progressed and their social roles allow for more independence. However, TA adults differ from older adults in that their neurocognitive development is not complete, and their social roles and institutional ties remain in flux. TA adults undergo consequential shifts in their circumstances. They experience greater independence from caregivers and childhood support systems, face increasing societal expectations of self-sufficiency, and continue self-exploration and experimentation, as they are yet to take on full adult responsibilities related to lifelong roles in occupations, partnerships, and as caregivers [2–6].

During this critical life phase, TA adults are more likely to use substances and have higher prevalence of substance use disorder (SUD) than adults aged 26 or older (14.4% vs. 7.2% in 2019). Paradoxically, they are less likely to receive specialty treatment for SUD than adults aged 26 or older (7.4% vs. 14.2% in 2019) [7]. Not only is TA adulthood a time of increased risk of developing SUD but also a time when prolonged exposure to substances can have lasting effects on brain development and future role functioning [8, 9]. Brain development extends into the mid-20s, during which time neurological areas associated with goal-seeking, emotional processing, and self-regulation continue to mature. The brain reward system is more developed than the inhibitory system among TA adults, contributing to potentially more harmful substance use and addiction [10–12].

Currently, the United States is experiencing an epidemic of opioid use disorders (OUD), including an opioid and polysubstance overdose crisis, increasingly among TA adults [13–15]. OUD are chronic conditions that require long-term treatment engagement for the best prognosis [16–20]. Individuals with OUD have high mortality, morbidity, and low remission, with abstinence rates of about 30% ten years after beginning care [21]. Over the past few years, the most significant increase in fatalities due to drug overdose was seen in cases involving illicitly-manufactured fentanyl and its analogues, with an average increase of 71% each year from 2013 to 2017 (whereas overdose deaths caused by prescription opioids and heroin have remained constant or declined, respectively) [22]. Notably, opioid-related mortality is highest among younger individuals (age 20 to 40 years) [23]. Additionally, prevalence of heroin use has more than doubled among TA adults in the past decade [24], with a significant increase in heroin overdose-related hospitalizations among 20–29 year olds in recent years [23]. The median age of onset for first heroin use, dependence, and treatment seeking for OUD patients is between 18–24 years of age, further underscoring the importance of emerging adulthood in OUD progression and treatment [25].

From 2012 to 2019, the number of TA adults receiving OUD treatment under New York State (NYS) Medicaid has increased more than 60%. Yet, TA adults often fall between two distinct treatment systems for SUD, most often placed in settings that are better tailored for adults, and where younger individuals feel out of place due to their unique social circumstances, such as having a shorter history of substance use and disorder [26], contributing to suboptimal treatment outcomes [27, 28].

Both the American Academy of Pediatrics and the American Society of Addiction Medicine recommend that medication be used in the treatment of young people with OUD [29–32]. Despite these recommendations, TA adults with OUD are less likely to receive MOUD than older adults [33–36]. In studies of young people with a diagnosis of OUD and covered by public and commercial insurance, one in four individuals received medications for OUD within six months of diagnosis [34, 35]. Only two randomized controlled trials of MOUD have been conducted specifically with TA adults and found that longer duration of MOUD (only 8–12 weeks in the trials) had improved outcomes over a shorter duration of MOUD [37, 38]. Studies generally find that longer retention in treatment is associated with improved outcomes [39–44], suggesting that stronger engagement in earlier treatment phases can lead to a better prognosis for TA adults [37, 38, 45–52].

Within SUD specialty treatment, MOUD increases treatment retention among TA adults [34, 53, 54]. However, TA adults generally have lower retention in specialty treatment than older adults [54, 55]. Even when MOUD is integrated into treatment, younger individuals are less adherent and more likely to leave treatment than older individuals [20, 27, 51, 56, 57]. Recent qualitative research highlights that TA adults acknowledge the life-saving potential of MOUD. Yet, they perceive receiving MOUD as stigmatizing and express ambivalence regarding MOUD, including fear of experiencing withdrawal symptoms, potential adverse effects, uncertainty regarding length of treatment, as well as concerns that MOUD might undermine self-sufficiency [58], which serves as a crucial marker of one’s transition to adulthood. There is a scarcity of studies of OUD treatment quality designed specifically for TA adults [59]. Observational studies of longitudinal cohorts are needed to identify if there are specific factors associated with use of MOUD, retention on MOUD, and adverse events related to treatment among TA adults [60].

Substance use and treatment for SUD occur within a broad social ecological context where the interplay of individual, community, and structural-level (including treatment program organizational) factors impact substance use and SUD treatment outcomes [61, 62]. Factors above the level of the individual, referred to as “social determinants of health,” such as structural racism and poverty, are potent fundamental causes of health inequalities [63].

TA adults have distinct individual-level characteristics that affect treatment engagement [4, 6, 64, 65]. They are more likely to have family members pressuring treatment [4, 64, 66, 67], and/or be involved with the criminal justice system [4, 26, 68, 69]. Criminal justice agencies and actors (e.g., judges and correctional staff) historically have been opposed to MOUD, preferring instead to rely on non-pharmacologic, non-evidence-based treatment approaches [70–73]. Furthermore, barriers to engagement, including lack of transportation or treatment programs that are high threshold settings, requiring frequent attendance at clinics and participation in highly structured protocols, challenge TA adults [60, 65, 67, 74–76]. TA adults are generally at ease interacting through modern telecommunications [6], with emerging shifts in telehealth that were prompted initially by the COVID-19 pandemic now offering new opportunities for treatment tailoring for this age group [77].

TA adults’ response to treatment also is affected by community-level factors that influence health and how they may engage with systems of care [78]. Variation in use of MOUD is associated with community social capital and local availability of programs offering MOUD [79]. MOUD is less available outside urban areas and often requires longer travel times that can be a barrier [74–76]. TA adults often contend with peers who use substances, local easy availability of substances, residential instability, hostile experiences with local law enforcement, and a lack of public transportation [80, 81]. Many TA adults from marginalized communities grapple with disparities in access and quality of care due to socioeconomic privation, racial/ethnic segregation and discrimination, and long-held community mistrust of medical and other institutions [67, 82–86].

Organizational-level factors also contribute to quality of care for TA adults [87]. Treatment programs that offer MOUD typically are larger organizations, hospital-affiliated, for-profit, and employ professional staff with advanced degrees (e.g., physicians, master’s level trained staff) [88, 89]. Data indicate that stigma of MOUD by staff in these healthcare settings has an impact on patients’ use of MOUD, even in programs that describe having a person-centered approach [90, 91]. Many specialty programs do not offer pharmacotherapy to youth [92], which has been associated with a lack of understanding of how to respond to the unique needs of these youth as they age into TA adults [93]. The impact of treatment program organization (e.g., program size and type), staffing (e.g., professional degrees), and clinical processes (e.g., use of telehealth, counseling modalities) on treatment quality practices and outcomes remains an area of ongoing exploration.

Considering the distinct circumstances and needs of TA adults, researchers and experts increasingly have called for additional research aimed at enhancing the quality of OUD treatment for this population [57, 60, 64]. Specific areas requiring investigation include strategies to improve MOUD access, engagement, and retention [94]. We extend prior studies by proposing a cohort-specific study that examines these questions using a social-ecological framework encompassing individual, community, and treatment program organization levels [18, 19, 34, 95].

## Materials and methods

### Conceptual framework

As an interdisciplinary team of social scientists, clinical psychologists, and physicians, we recognize that the quality of treatment and care for SUD is structured by the interplay of individual, community-level, and treatment program organizational dynamics. As such, our study’s conceptual framework integrates key principles from the field of social ecology and the Donabedian healthcare quality framework [61, 62, 96–98], guiding our research questions and analysis. Fig 1 below depicts the conceptual framework. Primarily, we recognize the importance of considering individual characteristics (e.g., age, comorbidities) alongside the social and built environments. Second, we acknowledge that environments have a multi-level impact on treatment access and quality of care. For our study, we explore how program structural characteristics (e.g., program size and type) and clinical processes (e.g., use of telehealth; counseling modalities) structure outcomes, conditional on individual and community characteristics (e.g., socioeconomic status, racial/ethnic composition). Third, we incorporate a longitudinal perspective in our analysis to assess explicitly the evolving impact of individual, treatment program, and community-level factors on treatment quality practices and outcomes over several years. Fourth, we evaluate the quality of OUD-related treatment provided by organizations through the Donabedian framework, focusing on three key processes: 1) structural or institutional factors associated with capacity to provide care; 2) clinical protocols––namely processes––that guide interactions between staff and patients; and 3) outcomes, that is, whether patients achieve the goals for which they entered treatment [96–98].

**Fig 1 pone.0297567.g001:**
[figure not shown]
Social ecological and Donabedian conceptual framework.

### Study design and aims of the study

Our study introduces a retrospective, longitudinal cohort design to assess treatment quality practices and outcomes among TA patients with OUD in NYS using administrative data from 2010 through 2025. We will combine Medicaid claims and encounter data with data from the Client Data System (CDS), a state registry of treatment episodes in licensed SUD treatment programs. CDS is an Office of Addiction Services and Supports (OASAS) treatment registry that all licensed providers of SUD treatment in the state of New York use to enter admission and discharge data. Data include demographics (e.g., age, race/ethnicity, and marital status), level of functioning (e.g., housing status, health status, and comorbid mental health), criminal justice status, recent history and frequency of substance use, and recent SUD treatment history. This registry data will supplement information from the Medicaid data with additional socio-demographic and clinical information as well as SUD treatment that was not funded by Medicaid. Therefore, despite fragmentation in funding sources, the combination of these administrative data sets will yield a more inclusive record of treatment episodes. Through this targeted, innovative approach, we intend to identify the diverse treatment outcomes within this specific demographic across different program organizations and communities. The study has been reviewed by the Institutional Review Board of NYU Grossman School of Medicine (#s22-00914) and meets the criteria for exemption under 45 CFR 46.104(d). Study findings will be disseminated via national and international conferences, reports, and peer-reviewed publications.

#### Aim 1. Quantify the associations between MOUD use and individual, community, and program characteristics

Our first aim involves conducting an analysis of associations of MOUD use among TA adults and psychological and social determinants of health at the individual, community, and program organizational level. Using the CDS and Medicaid claims from NYS, we will assess the impact of demographic data (e.g., race/ethnicity, criminal justice involvement), housing status, comorbid mental health diagnoses, and community-level indicators (e.g., program availability, the social vulnerability index) on MOUD use. Additionally, we will examine the relationship between MOUD use and treatment program organizational characteristics, such as program size and type, telehealth volume, and integrated mental health treatment. We also will explore the influence of a range of factors on the use of different MOUD options (e.g., buprenorphine, methadone, or XR naltrexone) at individual, program, and community levels.

#### Aim 2. Assess program organizational characteristics associated with improved adherence and retention in OUD treatment, while accounting for individual and community factors

Our second aim focuses on identifying organizational factors that may be associated with improved medication adherence and retention in OUD treatment among TA adults. We will evaluate the impact of program structural factors (e.g., program size and type), program staff characteristics (e.g., professional degrees), and clinical process measures (e.g., use of telehealth, counseling modalities) on medication adherence and treatment retention, adjusting for individual and community-level characteristics.

#### Aim 3. Examine the association between program organizational characteristics and adverse OUD-related events (AE) such as overdose, while accounting for individual and community factors

Our third aim centers on investigating the nexus between program organizational characteristics and OUD-related adverse events among TA adults including SUD-related emergency department visits or hospitalizations, including for overdoses, and increases in levels of SUD care. We will examine the association between program structural factors (e.g., program size and type) and AE outcomes. Additionally, we will examine how program staff characteristics (e.g., professional degrees) impact AE. We also will explore the association between clinical care process measures (e.g., use of telehealth, counseling modalities) and AE outcomes.

### Sample

The study cohort will be drawn from combined Medicaid and CDS data and will include approximately 65,000 individuals ages 18 to 25 whose first treatment episode for OUD in Medicaid occurs in 2012 or later—that is, not preceded by a prior OUD-related treatment episode in 2010 or later. Individuals who are co-insured with Medicare (some people under 65 with certain disabilities or conditions) will be excluded because not all their healthcare events are represented in the Medicaid claims data. We estimate that approximately 5,000 individuals will meet these criteria each year. Our link rate among all Medicaid enrollees with OUD ages 18–25 is 93%. The demographic and clinical profile is expected to be generally stable across years. Each year we will select TA adults receiving their first treatment for OUD. Once someone has joined a cohort, that person is retained in the analytical dataset in all future years. By using the first treatment episode in Medicaid as our index episode for a young cohort, we are identifying individuals early in their OUD treatment continuum of care. We estimate that about 26,000 TA adults will enter treatment after the COVID-19 public health emergency related telehealth and other measures take effect.

### Analysis

The study uses rigorous methods to address questions about multilevel factors associated with MOUD use, retention, and adverse event mitigation. Table 1 below outlines measures aligned with the social ecology framework and data sources. Baseline patient, program, and community characteristics will be assessed at admission, while ongoing treatment and healthcare measures will be assessed monthly. We also will compare pre- and post-COVID-19 treatment patterns to examine care innovations on retention and outcomes, like telehealth and flexibility in methadone take-home doses. We present an outline of the analytical approach, specifying the strategies we intend to employ for each of our three aims.

**Table 1 pone.0297567.t001:** Summary of outcome and predictor variables and sources by level.

Concept	Variables	Source
** *Individual Baseline Characteristics* **		
Demographic	Client age; race/ethnicity; gender; education; housing status; employment; criminal justice involvement; SNAP; subsidized housing	OASAS Medicaid
Clinical complexity	Mental health conditions: serious mental health conditions (e.g., schizophrenia); PTSD; ADHD; chronic physical conditions; non-cancer pain conditions; HIV; HCV; opioid analgesic prescription	Medicaid
Substance Use Patterns	Age of onset; opioid use; other substances used (alcohol, stimulants (methamphetamine/cocaine/prescription stimulants); cannabis, synthetic cannabinoids); frequency of use; and injection drug use (IDU)	OASAS
Prior Healthcare Utilization	History of use of outpatient; inpatient; emergency department	Medicaid
** *Individual-level Treatment Process* **		
Psychosocial Interventions*	Behavioral treatment (i.e., group, individual, peer, or family counseling); telehealth; toxicology screening; treatment for mental health conditions; Medicaid reimbursed transportation; harm reduction supports; recovery center supports; youth clubhouse supports	Medicaid
Medication for OUD (MOUD)*	Use of medication for opioid use disorder (MOUD); MOUD option: methadone, buprenorphine, XR naltrexone; buprenorphine formulation and dose; change in dose from prior time period; days of supply	Medicaid
** *Treatment Program Organizational Characteristics* **		
Structure	Specialty opioid treatment program; program size (i.e., annual patient volume); % of TA adults among all clients; % OUD among clients; type (i.e., inpatient, outpatient); hospital system affiliation; integrated license for mental health services	OASAS Medicaid
Staffing	Number of staff; staff professionalization (e.g., degrees); gender and race/ethnicity; client-to-staff ratio	OASAS
Clinical Process	% MOUD (e.g., methadone, buprenorphine, XR naltrexone) among OUD clients; average monthly volume claims for individual, group, peer, and family counseling; average monthly volume claims for telehealth use; monthly volume for toxicology screening	Medicaid

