*Aim 1b*: *Associations with program organizational characteristics*. Second, we will focus on examining the connection between MOUD use and treatment program organizational characteristics (e.g., program size and type, volume of telehealth, integrated mental health treatment). Like Aim 1a, we will use GLMMs to analyze treatment program measures. These models will be adjusted for age, sex, race, other individual and community baseline measures, and other time-varying covariates (as detailed in the measures table). For aims 1a and 1b, estimates of odds ratios and their corresponding 95% confidence intervals will be reported.

*Aim 1c*: *Associations with MOUD options*. Third, we will investigate the factors linked to the use of different MOUD options (e.g., buprenorphine, methadone, or XR naltrexone) at individual, program, and community levels. To explore the association between medication option, provider proximity, and racial/ethnic patient characteristics, we will employ mixed effects multinomial logistic regression, while adjusting for individual, program, and county level covariates.

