*Aim 2a*: *Program structural factors and adherence and retention in OUD treatment*. First, we will investigate the association between program structural factors (e.g., program size and type) and adherence and retention, guided by the hypothesis of adjusted hazard ratios being equal to 1.

*Aim 2b*: *Program staff characteristics and adherence and retention*. Second, we will examine the relationship between program staff characteristics (e.g., professional degrees) and adherence and retention, guided by the hypothesis of adjusted hazard ratios being equal to 1.

*Aim 2c*: *Clinical care process measures and adherence and retention*. Third, we will analyze the association between clinical care process measures (e.g., use of telehealth, counseling modalities) and adherence and retention, guided by the hypothesis of adjusted hazard ratios being equal to 1.

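### Program counseling, telehealth and toxicology exposures are claim volumes without a patient-time denominator, so where programs differ in retention, Aim 2c would tend to show a spurious association

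*Protocol article*

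**What the plan says.** In Table 1, under treatment program organizational characteristics, the clinical process row gives the counseling, telehealth and toxicology measures as "average monthly volume claims for individual, group, peer, and family counseling; average monthly volume claims for telehealth use; monthly volume for toxicology screening". None of the three is divided by patients or patient-time. The first measure in that row does have a denominator: it is the percentage receiving "MOUD (e.g., methadone, buprenorphine, XR naltrexone) among OUD clients". The structure row defines "program size (i.e., annual patient volume"), so volume there means a total count. Aim 1b again names "volume of telehealth" as a program characteristic.

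Under Aim 2c, "we will analyze the association between clinical care process measures (e.g., use of telehealth, counseling modalities) and adherence and retention", against a null hazard ratio of 1. Table 1 defines retention as days in the treatment episode. The Aim 2 events are MOUD discontinuation after initiation and treatment completion. Program characteristics are assessed at admission and are not marked as time-varying.

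**The concern.** A program's monthly claims depend on how much care each patient receives and on how many patients are enrolled that month. The second factor grows with length of stay, which is what Aim 2 studies. A program that keeps patients longer for any reason bills more counseling, telehealth and toxicology claims, even if each patient receives the same care per month as elsewhere.

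Aim 2c is meant to learn about care delivered: use of telehealth and counseling modalities. With volume as the exposure, a hazard ratio below 1 for MOUD discontinuation could reflect care intensity or simply the program's existing retention pattern, and the analysis could not tell them apart. Telehealth is a headline question of the study, and the results are meant to inform clinical and public health decisions. In Aims 1b and 3c the same volumes partly stand in for program size.

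**Working it through.** The article gives no power or effect figure for Aim 2, so there is no stated figure to reproduce.

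**Identities.** Let *a* be admissions per month, *L* mean stay in months and *s* claims per patient-month.
- Census = *a* × *L*
- Monthly volume *V* = *a* × *L* × *s*
- Annual patients *N* = census + 12*a* = *a*(*L* + 12)

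**Two programs with identical care (illustrative inputs).** Both have *a* = 20 and *s* = 4; *L* is 3 or 6.

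| | *L* = 3 | *L* = 6 | Ratio |
|---|---|---|---|
| Census | 60 | 120 | 2.0 |
| Monthly volume | 240 | 480 | 2.0 |
| Annual patients | 60 + 240 = 300 | 120 + 240 = 360 | 1.2 |
| Volume / annual patients | 0.80 | 1.33 | 1.67 |
| Volume / census | 4 | 4 | 1.0 |

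Only the patient-month denominator shows that care is the same.

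**Why size adjustment does not help.** Substituting *a* = *N*/(*L* + 12) gives *V* = *N* × *s* × *L*/(*L* + 12). At fixed *N*, volume still moves with *L*. On the log scale the elasticity is 12/(*L* + 12), which is 12/17 = 0.706 at *L* = 5. Adjustment removes most of the size variation but leaves about 70% of the stay variation.

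**Size under a true null.** Assumptions not in the documents: 400 programs with 150 patients each; log-normal admissions (SD 0.6), mean stay (median 5 months, SD σ) and claims per patient-month (SD 0.4), all independent; program hazard 1/*L*; 200 runs per setting. The approximate size-adjusted slope per log unit of volume is −0.706σ² / (0.4² + 0.706²σ²). At σ = 0.2 this is −0.0282/0.1799 = −0.157; per doubling, exp(−0.157 × 0.693) = 0.897. At σ = 0.4 it is −0.113/0.240 = −0.471, giving 0.72.

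| σ | HR per doubling, unadjusted | HR per doubling, size-adjusted | p < 0.05 (size-adjusted) | HR with claims per patient-month |
|---|---|---|---|---|
| 0 | 1.00 | 1.00 | 8% | 1.00 |
| 0.1 | 0.99 | 0.97 | 74% | 1.00 |
| 0.2 | 0.95 | 0.90 | 100% | 1.00 |
| 0.3 | 0.90 | 0.81 | 100% | 1.00 |
| 0.4 | 0.85 | 0.73 | 100% | 1.00 |

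Adjusting for annual patients makes the artefact larger.

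**Second design.** About 65,000 patients, exposure built only from past patients (to match assessment at admission), mean stay 6 months, claim intensity log-SD 0.5, robust standard errors. These hazard ratios are per SD of log volume, so they are on a different scale from the table. With 500 programs and between-program log-hazard SD of 0, 0.1, 0.2 and 0.4, the size-adjusted HR was 1.00, 0.971, 0.893 and 0.69, with false-positive rates of 4%, 35%, 92% and 100%. With 100 programs at SD 0.2 the rate was 52%. At SD 0.2 with 500 programs, the HR ran from 0.715 to 0.963 as the log-SD of claim intensity went from 0.25 to 1.0. Dividing by annual patients instead still gave 0.95 with 92% false positives. Claims per patient-month gave 0.996 to 1.001, with 4% to 13% false positives.

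**The case against.** A reader might infer that Aim 2c is bound to find that counseling or telehealth improves retention. The documents do not support that, for these reasons:

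- **The bias is conditional.** It needs differences in retention between programs that remain after adjustment. With none, the hazard ratio is 1.00. The article gives no size for such differences, although looking for program factors behind retention is the premise of Aim 2.
- **The simulated model is not the planned one.** It adjusts only for annual patient volume. Table 1 also lists program type, specialty status, hospital affiliation, number of staff and client-to-staff ratio. If the ratio counts current clients, staff × ratio equals census. Adding both in log form with that definition returned the hazard ratio to 1.00, with about 3% to 6% false positives. With linear terms or noisy staffing data, bias remained (about 0.91 to 0.94 at SD 0.2). The article fixes neither the ratio's definition nor the functional form, so the protection is possible but not assured.
- **The exposure does not contain the patient's own outcome.** With assessment at admission, the path runs only through the program's persistent retention pattern. That path remains. Centering is within county, and program random effects appear only in a sensitivity analysis and would be correlated with the exposure.
- **Benefit is not the natural reading for both events.** A lower hazard of treatment completion is not plainly an improvement.
- **Individual care is also measured.** Table 1 lists time-varying counseling, telehealth and toxicology for each patient. This does not repair the program-level exposure that Aim 2c names.
- **Averaging could mean per client.** The wording leaves some room, and a per-enrolled-client-month definition would largely remove the problem. But neighbouring measures state their denominators, volume is used as a count for program size, and the toxicology item is not called an average. The natural reading is a total averaged over months.

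The article's caution about causal inference concerns program selection. It does not address an exposure tied to retention by construction.

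**Conclusion.** The point stands in its conditional form and should be fixed. As defined, the three program measures combine care intensity with census. Where retention differs between programs after adjustment, Aim 2c would tend to show a spurious association, and for MOUD discontinuation an apparently protective one to the extent that MOUD persistence tracks length of stay. Annual patient volume does not correct it; staffing covariates might in part. The true size cannot be derived from the documents. The range of about 1.00 to 0.73 per doubling rests on the assumed spreads of stay (0 to 0.4) and claim intensity (0.4) and on leaving out the other listed covariates. It shows what could happen and does not predict the study's estimate. In Aims 1b and 3c the consequence is milder: an effect of volume is partly an effect of program size.

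**What to change.** In the clinical process row of Table 1, define counseling as claims per enrolled patient-month by modality, telehealth as the share of visits delivered by telehealth, and toxicology as tests per enrolled patient-month. Compute each over a fixed window before the index admission (for example the prior 12 months), excluding the index patient's own claims. Keep program size as a separate variable, and do not use annual patients as the denominator.

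Add a version restricted to a fixed early-treatment window. If claims cluster at intake, the per-patient-month rate is itself biased slightly the other way: with 8 extra intake claims per admission (assumed), the null hazard ratio per SD was 1.027, with about 50% false positives.

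The cost is small. The denominator comes from Medicaid and treatment-registry data already held, and the article reports that no analysis had begun, so the definition could still be prespecified at that point. The downside is noisier rates in small programs, which need a minimum-denominator rule.
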